**Table 2 Tab2:**
[figure not shown]
Timeline {13}

**Table 3 Tab3:**
[figure not shown]
Schedule of assessments {13}

### Outcome measures and follow-up {12}

#### Primary outcome

The primary outcome will be level pain using Numeric Pain Rating Scale (NPRS). The NPRS is a segmented numeric version of the visual analog scale (VAS) in which a respondent selects a whole number (0–10 integers) that best reflects the intensity of his/her pain. A reduction of ≥ 2 points in NPRS is considered clinically significant pain relief [40]. This outcome will be measured at baseline at the moment of clinical interview and decision to recruitment and CI singed. This outcome will be measured again after the second intervention at 30 days, 3 months, 6 months, and 12 months after the intervention.

### Secondary outcomes

The secondary outcomes include the following: Oswestry Low Back Pain Disability Scale (ODS) [41–43], Scale for Mood Assessment (MOAS) or Mood Rating Scale (MRS) [in Spanish original name *Escala de Valoración del Estado de Ánimo (EVEA)*] [44], Quality of Life (SF 12) test [45–47], and *Douleur Neuropathique 4 questions* (DN4) scale [48, 49]. They will be measured at baseline and after 1 month, 3 months, 6 months, and 12 months of the intervention (Additional file 1: Annex I).

The total duration of the randomized placebo-controlled study is expected to be 36 months, including 24 months for patient recruitment and 12 months for final patient follow-up.

### Data collection {18a} {18b} {19} {27}

At baseline, patient demographics and prior failed therapies will be documented, including frequency, duration, type, and compliance, as well as magnetic resonance imagining (MRI) and electromyography (EMG) diagnostic tests. Documentation of analgesic use for the treatment of LLR will include frequency, dosage, and duration. All baseline and post-procedural follow-up points will include reported outcomes documented through completing the NPRS, ODS, MOAS, SF-12, and DN4 questionnaires and documentation of narcotic and non-narcotic analgesic medication usage. Device and procedure-related adverse events and all serious adverse events will be documented throughout the study period (Table 3).

The data collected will be stored in locked cabinets, and only the main researcher will have access to this information. Data will be recruited in a computer spreadsheet with password protection to ensure confidentiality. To ensure no error, the spreadsheet will be monthly monitored and audited by a researcher who is blind to the participants’ group allocation and has no conflict of interest.

All patients who leave the study for any reason will no longer have their data collected.

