### Monitoring, safety, and quality control

The primary safety endpoint is the incidence of device- and/or procedure-related adverse events, which will be compared statistically between the randomized groups using proportions of patients experiencing such an event. The endpoint will be met if this event rate is not significantly greater with ACS than with PhS. All study-related adverse events will be monitored and reported, including seriousness, severity, treatment, and relationship to the study device/procedure. Adverse events collected in this study will be determined by the mine investigator to be specifically related to the products or procedures used in the 2 treatment groups or one that is determined to be a serious adverse event {22}.

To date, all published studies with ACS have shown high safety rates and no side effects for what ACS product itself represents. Even so, any intervention can lead to an adverse effect, so their monitoring will be an essential condition in this protocol {11b}.

Once the study has started, given that the inclusion of patients will be progressive over time as they are recruited, just in case there is a worsening of pain of more than 25% in more than 50% of the patients, the study would be reconsidered and the recruitment would be stopped to analyze the data and check if the worsening is in patients whom the ACS therapy was applied. If this were the case, the study would be definitively stopped and a report would be given to the laboratory. The author responsible for the study will carry out this audit if necessary. The main investigator together with the rest of the authors will make the decision to terminate the trial early {17b} {21a}.

Any other adverse effect as far as the interventions are concerned will be collected and analyzed (if necessary, the second intervention would be canceled, and the patient would be withdrawn from the study) {11b} {21b}.

The main investigator is the only person who will be in charge of follow-up with clinical interviews at 30 days, 3 months, 6 months, and 12 months. A schedule of visits will be established for each patient for their greater adherence to the study and not to delay follow-up. Apart from the following-up visit controls, the patients will provide from a telephone number of pain unit for any doubts, changing pain characteristics, or new interventions they will receive. In that way, it provides an improving of adherence to protocol of the study {11c}.

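### Data collection stops when a patient leaves for any reason, with no exception for safety data, so adverse events and their outcomes after withdrawal go unrecorded

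*Protocol article*

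**What the plan says.** Three statements in the protocol article bear on safety data after a patient leaves.

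- **Data collection, the promise:** "Device and procedure-related adverse events and all serious adverse events will be documented throughout the study period".
- **Data collection, the cut-off**, at the end of the same section: "All patients who leave the study for any reason will no longer have their data collected".
- **Monitoring, safety, and quality control, the link between them:** for an adverse effect of the interventions, "if necessary, the second intervention would be canceled, and the patient would be withdrawn from the study".

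The Monitoring section also sets what is recorded about an event: "All study-related adverse events will be monitored and reported, including seriousness, severity, treatment, and relationship to the study device/procedure". On adverse effects of the interventions it adds: "Any other adverse effect as far as the interventions are concerned will be collected and analyzed".

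It then defines the endpoint: "The primary safety endpoint is the incidence of device- and/or procedure-related adverse events". The groups are compared on the proportion of patients with such an event, and the endpoint is met if the ACS rate is not significantly higher than the saline rate.

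Two other sections contain related exits. Statistical analysis ends outcome collection for a patient who drops out of treatment, although the analysis is by intention to treat. Pain management takes a patient out of the trial after surgery or infiltration in the treated area and bars use of that patient's data from that date.

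**The concern.** The cut-off covers every patient, every reason for leaving and all data. An adverse effect can itself be the reason. Followed as written, the rule can end safety observation for a patient who has just had an adverse effect, at a time when the event may still be open.

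Two things are at stake:

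- **The safety description.** The eventual outcome of an event, treatment given after withdrawal and any later serious event would be missing for patients in whom they are of most interest.
- **The primary safety endpoint.** A patient who leaves before any related event cannot contribute one afterwards. The success criterion is the absence of a significant excess, so events missed with ACS favour meeting it.

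**Working it through.** The plan states no figure on this point that could be reproduced. The check is a reading of the sections together, with a little arithmetic for scale.

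**Step 1: is safety data exempt from the cut-off?** The Data collection sentence contains no exemption. Neither the Monitoring section nor any other part of the article provides for recording events, or following an open event, after a patient has left. The Monitoring section does give patients a pain unit telephone number, but as an aid to adherence during follow-up.

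**Step 2: what is lost, by type of leaver?**

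| Patient | Recorded | Not recorded after leaving | Effect on primary safety endpoint |
|---|---|---|---|
| Withdrawn because of a related event | The event, with severity, and treatment up to withdrawal | Later course, outcome, later treatment, any later serious event | None: already counted once |
| Leaves for another reason, before any related event | Nothing to record yet | Any later related or serious event | A later first related event goes uncounted |

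**Step 3: direction of the effect on the endpoint.** Let n be the patients in an arm, L the number who leave before a first related event, and q the share of those who would later have had one. No section removes leavers from the comparison, so they are taken to stay in the denominator. Then

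observed proportion = full-follow-up proportion − (L × q) / n.

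The distortion of the difference, ACS minus saline, is −(L_ACS × q_ACS)/n_ACS + (L_PhS × q_PhS)/n_PhS. With equal arms and similar q, it is negative when more such patients leave the ACS arm. The criterion is then easier to meet. If more leave the saline arm, the effect is reversed.

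**Step 4: scale.**

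- Sample size section: 70 patients, 35 per arm, 10% loss to follow-up. 0.10 × 70 = 7 patients in all, or 3.5 per arm if spread evenly.
- With 35 per arm, each uncounted patient lowers that arm's proportion by 1/35 = 2.9 percentage points.
- L and q are not given for either arm. The 10% covers loss to follow-up from all causes; it is not a rate of withdrawal for adverse effects or of leaving before a first event. Seven patients is therefore an outer scale on the plan's own expectation, not an estimate.
- Trial intervention and blinding section: the second procedure is 14 days after the first. A patient withdrawn between the two has at most about two weeks of safety observation after treatment, against about 12 months for one who completes follow-up. The article does not say how many such patients to expect.

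**The case against.** The strongest case on the other side is that this is a loose sentence in a condensed article, with little consequence.

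**A reader might infer that the two Data collection statements are strictly incompatible.** The text does not establish that. If the study period means each patient's own time in the study, both can stand. The article does not say which meaning applies, and on either reading nothing is recorded after a patient leaves.

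**A reader might infer that the severity of the event behind a withdrawal is lost.** The Monitoring section contradicts this: the effect is collected and analysed, and severity is among the items reported.

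**A reader might infer that patients withdrawn for a related event bias the primary safety endpoint.** They do not. The endpoint counts patients, and these are already counted. The bias argument holds only for those who leave before a first related event.

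**A reader might infer that leavers are dropped from the safety comparison, or try to put a number on the missed events.** No section excludes them from that comparison, and no split of withdrawals by arm or later event rate can be taken from the article.

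It is also fair to say that withdrawal for an adverse effect is conditional, that the schedule of assessments (Table 3) is not visible here, and that a fuller protocol may describe how open events are followed. These points lower the weight of the concern but do not remove it. The cut-off is a stated rule, worded without exception, rather than a detail left out for brevity.

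**Conclusion.** The point holds in a limited form. As written, the article ends safety data collection for every patient who leaves, including one withdrawn for an adverse effect. The loss is the later course and outcome of the triggering event and any later serious event. For the primary safety endpoint, the loss is confined to patients who leave before a first related event. It favours meeting the criterion if more of them leave the ACS arm.

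The size cannot be computed from the article and may be small. The conclusion about direction assumes that leavers stay in the denominator and that the share who would later have an event is similar in the two arms. The gap in safety follow-up depends on neither assumption, nor on how the study period is read.

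**What to change.** Limit the Data collection sentence to patients who withdraw consent to data collection. For all others who leave, or whose second intervention is cancelled, state that:

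- related and serious adverse events continue to be recorded to month 12;
- events still open on leaving are followed to their outcome;
- contact is through the existing visits or the pain unit telephone line.

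Reconcile the Data collection, Monitoring, Statistical analysis and Pain management sections, so that stopping treatment, leaving the study and withdrawing consent to data collection are kept apart. This concerns data collection only; it leaves open when treatment should be stopped or a patient withdrawn.

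The cost is an amendment to protocol and consent wording and a few extra contacts, for about 7 patients if the planned loss is a guide. Some who leave will not be reachable, so the gap would be reduced rather than closed.

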### Monitoring, safety, and quality control

The primary safety endpoint is the incidence of device- and/or procedure-related adverse events, which will be compared statistically between the randomized groups using proportions of patients experiencing such an event. The endpoint will be met if this event rate is not significantly greater with ACS than with PhS. All study-related adverse events will be monitored and reported, including seriousness, severity, treatment, and relationship to the study device/procedure. Adverse events collected in this study will be determined by the mine investigator to be specifically related to the products or procedures used in the 2 treatment groups or one that is determined to be a serious adverse event {22}.

To date, all published studies with ACS have shown high safety rates and no side effects for what ACS product itself represents. Even so, any intervention can lead to an adverse effect, so their monitoring will be an essential condition in this protocol {11b}.

Once the study has started, given that the inclusion of patients will be progressive over time as they are recruited, just in case there is a worsening of pain of more than 25% in more than 50% of the patients, the study would be reconsidered and the recruitment would be stopped to analyze the data and check if the worsening is in patients whom the ACS therapy was applied. If this were the case, the study would be definitively stopped and a report would be given to the laboratory. The author responsible for the study will carry out this audit if necessary. The main investigator together with the rest of the authors will make the decision to terminate the trial early {17b} {21a}.

Any other adverse effect as far as the interventions are concerned will be collected and analyzed (if necessary, the second intervention would be canceled, and the patient would be withdrawn from the study) {11b} {21b}.

The main investigator is the only person who will be in charge of follow-up with clinical interviews at 30 days, 3 months, 6 months, and 12 months. A schedule of visits will be established for each patient for their greater adherence to the study and not to delay follow-up. Apart from the following-up visit controls, the patients will provide from a telephone number of pain unit for any doubts, changing pain characteristics, or new interventions they will receive. In that way, it provides an improving of adherence to protocol of the study {11c}.

As far as the samples are concerned, both the laboratory responsible for the ACS and the pharmacy of DUH will have a record of the samples and their transport and temperature. Each sample will have a special label (study code, randomization number) and will be guarded by the pharmacy upon arrival from the laboratory and when it is withdrawn by the investigator on the day of its use for injection.

The study will be carried out in the facilities of the DUH, a document of suitability of the facilities signed by the head of the Department of Anaesthesiology and pain unit. In the same way, a commitment document is attached by the Hospital’s Pharmacy Department for the control and monitoring of the study. The main investigator will take the responsibility to monitoring of the study. She will coordinate with the people in the laboratory, pharmacy, and pain unit. There is also a thesis director who will meet monthly with the author responsible for the study and running the trial day-to-day to provide organizational support. In conclusion, since the day-to-day task falls on the main investigator, she will be responsible for any important protocol modification and technical aspects of the trial as well as data collection, outcome analyses, and results. She will be in charge of notifying the rest of authors as well as laboratory and pharmacy {5d} {21a} {25}.

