**Methods:**

We plan to conduct a randomized controlled study to compare the efficacy of PRF therapy plus ACS versus PRF therapy plus physiological saline 0.9% (PhS) on the DRG to reduce neuropathic pain in patients with persistent lower limb radiculalgia (LLR) and to contribute to the functional improvement and quality of life of these patients.

Study participants will include patients who meet study the inclusion/exclusion criteria. Eligible patients will be randomized in a 1:1 ratio to one of treatment with PRF plus ACS (experimental group) or PRF plus PhS (placebo group). The study group will consist of 70 patients (35 per group) who have experienced radicular pain symptoms for ≥ 6 months’ duration who have failed to respond to any therapy. Both groups will receive PRF on the DRG treatment before the injection of the sample (control or placebo). Patient assessments will occur at baseline, 1 month, 3 months, 6 months, and 12 months after therapy.

The primary efficacy outcome measure is Numeric Pain Rating Scale (NPRS) responders from baseline to 12 months of follow-up using validated minimal important change (MIC) thresholds. A reduction of ≥ 2 points in NPRS is considered a clinically significant pain relief.

The secondary efficacy outcome measure is the proportion of Oswestry Low Back Pain Disability Scale (ODS) responders from baseline to 12 months of follow-up in the experimental group (PRF plus ACS) versus the placebo group (PRF plus PhS). ODS responders are defined as those patients achieving the validated MIC of ≥ 10-point improvement in ODS from baseline to 12 months of follow-up as a clinically significant efficacy threshold.

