**Discussion:**

This prospective, double-blind, randomized placebo-controlled study will provide level I evidence of the safety and effectiveness of ACS on neuropathic symptoms in LLR patients.

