### Sample size {14}

Based on the existing bibliography in relation to the treatment of pain by ACS treatment for other similar affections [32], it is estimated that accepting an alpha risk of 0.05 and a beta risk of 0.2 in a bilateral contrast, 35 subjects in the treatment group and 35 in the placebo group are needed to detect as statistically significant the difference between the proportion of patients with reduction pain of two points on the NPRS scale, which for the intervention group is expected to be 65%, and for the control group, it is expected to be 35%. A rate of loss to follow-up of 10% has been estimated.

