### Statistical analysis {20a} {20b} {20c} {18b}

A descriptive analysis will be carried out for all the data collected. The normality of the data will be studied using the Kolmogorov–Smirnov and Shapiro–Wilk tests. For continuous quantitative variables, descriptions of central tendency and dispersion will be presented: mean and standard deviation respectively in case the variables follow a normal distribution or median and interquartile range for those variables that are not normally distributed. For categorical (qualitative) variables, frequencies and percentages will be presented. The main outcome (improvement > 2 points) will be tested using a generalized linear mixed model (GLMM). The GLMM model fit will include a between-subject factor and will also include a random effect for the time (baseline, 1st month, 3th month, 6th month, and 12th month) and the interaction between group and time variables. The inclusion of the interaction terms allows for a formal test between the groups over time. For the other variables, the mean effects of the interventions and the differences between groups and their respective 95% confidence intervals will be calculated using regression linear mixed models for repeated measures, which will incorporate terms for the treatment groups, time, and interaction terms. Treatment coefficients versus time interactions will be equivalent to the estimates of the differences between groups. All models will be adjusted for chance imbalances in outcome between groups at baseline. There will also be analyses of the covariates collected, including age, gender, and duration of symptoms. The analyses will follow the principles of intention to treat, and no interim analyses will be performed. No additional analysis will be performed. If a patient drops out of treatment, no additional outcome will be collected. The significance level will be set at 5%, and SPSS for Windows will be used for the statistical analysis.

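### The primary safety endpoint counts as met when ACS is not significantly worse, with no margin or safety power, so at low event rates it would often pass a real excess

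*Protocol article*

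**What the plan says.** The protocol article's section on safety monitoring and quality control defines the endpoint as follows: "The primary safety endpoint is the incidence of device- and/or procedure-related adverse events, which will be compared statistically between the randomized groups". The comparison uses the proportion of patients with such an event. The success criterion follows directly: "The endpoint will be met if this event rate is not significantly greater with ACS than with PhS". The section names neither the test nor its sidedness. The Statistical analysis section sets a general 5% significance level.

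The Sample size section states that "35 subjects in the treatment group and 35 in the placebo group are needed to detect as statistically significant the difference" in the proportion of patients whose pain falls by two points on the NPRS, "accepting an alpha risk of 0.05 and a beta risk of 0.2 in a bilateral contrast". It assumes 65% versus 35% responders and 10% loss to follow-up, and does not mention adverse events. The article gives no numerical adverse event rate for either arm. It describes pulsed radiofrequency as having few complications and the ACS product as free of side effects in published studies.

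The abstract's Discussion says that the trial "will provide level I evidence of the safety and effectiveness of ACS on neuropathic symptoms in LLR patients".

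**The concern.** A test that fails to reject equality has not shown that there is no excess. Under this rule the endpoint is met either because ACS adds no harm or because there are too few patients and events to show the harm. The rule therefore becomes easier to pass as information is lost. The article also says, under Data collection, that data are no longer collected once a patient leaves. Under Monitoring, it allows a patient with an adverse effect to be withdrawn.

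The defect lies in a criterion that the protocol states, not in a detail left to an analysis plan; a plan that followed the protocol faithfully would carry it forward. At stake is a report that the primary safety endpoint was met when the data are compatible with a large excess of adverse events.

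**Working it through.** **The plan's own figure.** The 35 per arm is an efficacy number. With 65% versus 35%, two-sided 5% and 80% power, the pooled formula gives

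n = [1.960·√(2·0.5·0.5) + 0.842·√(0.65·0.35 + 0.35·0.65)]² / 0.30² = (1.386 + 0.568)² / 0.09 ≈ 42.4, so 43 per arm, or 43/0.9 ≈ 48 after 10% loss.

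The stated 35 does not reproduce from these inputs (a one-sided test without loss gives 34). That is a separate matter. The calculations below take 35 per arm as planned.

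**Inputs for the safety rule.** 35 per arm and the 5% level come from the article. The control event rate is an assumption, varied from 2% to 20%. The test and its sidedness are not stated, so Fisher's exact test and the uncorrected chi-square test are both shown, two-sided and one-sided at 5%.

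**Method.** With X events on saline ~ Bin(35, p_C) and Y on ACS ~ Bin(35, p_T), sum P(X=x)·P(Y=y) over all pairs with y > x and p ≤ 0.05. This is the probability of detecting the excess. The probability that the endpoint is met is one minus that sum.

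| Saline vs ACS | Detected, two-sided (Fisher / chi-square) | Met, two-sided | Detected, one-sided (Fisher / chi-square) | Met, one-sided |
|---|---|---|---|---|
| 2% vs 6% | 0.009 / 0.083 | 91.7–99.1% | 0.029 / 0.193 | 80.7–97.1% |
| 2% vs 8% | 0.030 / 0.172 | 82.8–97.0% | 0.079 / 0.319 | 68.1–92.1% |
| 5% vs 15% | 0.136 / 0.308 | 69.2–86.4% | 0.229 / 0.427 | 57.3–77.1% |
| 5% vs 20% | 0.328 / 0.517 | 48.3–67.2% | 0.454 / 0.632 | 36.8–54.6% |
| 10% vs 30% | 0.455 / 0.565 | 43.5–54.5% | 0.577 / 0.683 | 31.7–42.3% |
| 10% vs 40% | 0.785 / 0.852 | 14.8–21.5% | 0.867 / 0.915 | 8.5–13.3% |
| 20% vs 60% | 0.910 / 0.942 | 5.8–9.0% | 0.957 / 0.975 | 2.5–4.3% |

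If 10% are lost (35·0.9 = 31.5, so 31 per arm), two-sided detection of 5% vs 15% falls to 10–27% (met in 73–90%). For 5% vs 20% it falls to 26–47% (met in 53–74%).

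**Observed results that pass under every one of these tests.** The most easily significant of the four is the one-sided chi-square, with critical value 1.645.

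- 4/35 vs 1/35: pooled rate 5/70 = 0.0714; z = 0.0857/√(0.0714·0.9286·2/35) = 1.39. Not significant, so met. The Wilson limits are 0.045 to 0.260 and 0.005 to 0.145. The Newcombe 95% interval for the excess is 0.0857 − √(0.0689² + 0.1167²) to 0.0857 + √(0.1452² + 0.0235²), that is −5 to +23 percentage points.
- 6/35 vs 2/35: pooled rate 8/70 = 0.1143; z = 0.1143/√(0.1143·0.8857·2/35) = 1.50. Not significant, so met. The Newcombe interval is −4 to +28 points.

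**What 35 per arm could exclude with a margin.** For equal true rates p, one-sided 2.5% and 80% power, n = (1.960 + 0.842)²·2p(1−p)/m². At p = 5% this gives 299 per arm for m = 5 points, 75 for 10 and 34 for 15. At p = 10% it gives 566, 142 and 63, and 36 for 20 points. These rates and margins are illustrations only.

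**The case against.** Four points on the other side deserve weight.

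1. **The size depends on an assumed event rate.** A reader might infer that the rule would declare safety after any three- to four-fold excess, or in most scenarios of real harm. The documents do not support that. They give no event rate; the endpoint counts procedure-related as well as device-related events, and each patient has the full procedure twice. If background events are common, the rule detects a large ratio well, as the 10% vs 40% and 20% vs 60% rows show. Even at 5% vs 20%, the two-sided chi-square detects the excess slightly more often than not (52%). This stands and limits the claim to low event rates.

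2. **The test is unstated.** More striking counts such as 5/35 vs 0/35 or 7/35 vs 1/35 are tempting examples. They pass by two-sided Fisher (p = 0.054 and 0.055) but fail by uncorrected chi-square (p = 0.020 and 0.024) and by one-sided Fisher (p = 0.027 for both). They cannot be said to pass under the plan as written.

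3. **Safety review is wider than this rule.** All study-related events are reported with seriousness, severity and relationship, serious adverse events are documented throughout, and there is a separate stopping rule for worsening pain. This limits the harm but does not change what a met endpoint means.

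4. **The abstract's claim of level I evidence describes the randomised, double-blind design and does not cite the rule.** It is therefore not proof that the sponsor intends to rest the safety claim on non-significance alone.

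None of these points supplies a margin, a confidence limit or a safety power.

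**Conclusion.** The rule is wrong as written: it lets absence of significance stand as a met primary safety endpoint in a trial not sized for adverse events. That conclusion needs no assumption about rates.

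The size does need one. With a 5% control rate, 35 per arm and a two-sided 5% test, a true rate of 15% would pass in about 69–86% of trials and 20% in about 48–67% (57–77% and 37–55% if one-sided). At 10% vs 30% it would pass in about 43.5–54.5% (two-sided), and at 10% vs 40% in only about 15–22%. The supportable statement is that the rule would often, not always, pass a real excess when events are uncommon. The article's own description of the procedure and product suggests low rates but does not establish them.

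**What to change.** Delete the pass/fail sentence from the protocol's safety section. In its place, state that the number and proportion of patients with a device- or procedure-related adverse event will be reported per arm, with the risk difference (ACS minus saline) and its 95% confidence interval (for example Newcombe), and that a non-significant difference will not be read as evidence of safety.

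If the sponsor wants to keep a yes/no endpoint, define it as met only when the upper confidence limit of the risk difference lies below a margin that the sponsor fixes and justifies in advance, and state its power. Under the illustrative assumptions above, 35 per arm would have about 80% power only for a margin of roughly 15 points at a 5% event rate or 20 points at 10%, so a tighter margin would need more patients.

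The descriptive version costs a protocol wording change, carried into any analysis plan, and a weaker safety claim. It needs no new patients or data.
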